## Abstract

**Background:**

Given the increasing prevalence of non-alcoholic fatty liver disease, it is necessary to find an easy and cost-effective method in its management and treatment. Probiotics are a group of living microorganisms that might affect NAFLD through the intestinal-liver axis. The present clinical trial aims to examine the effect of probiotic yogurt consumption on liver enzymes, steatosis and liver fibrosis in patients with NAFLD.

**Methods:**

Sixty-eight patients with NAFLD will be recruited in this study. After block matching for sex, BMI and age, patients will be randomly assigned to receive 300 g/d probiotic yogurt containing 10^6^ cfu/g of Lactobacillus acidophilus and Bifidobacterium lactis strains or 300 g/d plain yogurt daily for 12 weeks and those in the control group would receive similar amounts of plain yogurts. Weight, height, and waist circumference will be measured at study baseline and after the intervention. Biochemical indicators including plasma glucose, serum insulin, lipid profile, liver markers (ALT, AST and GGT) will be examined at study baseline and at the end of the trial. Insulin resistance and insulin sensitivity will be determined using the HOMA-IR and QUICKI equation. The degree of steatosis and hepatic fibrosis will also be assessed at the beginning and end of the intervention by the same gastroenterologist using elastography with fibroscan.

**Discussion:**

Probiotics have been suggested as a new strategy in the management of NAFLD. Their effects might be mediated through intestinal microbiota modification and production of short-chain fatty acids. Consumption of probiotic-enriched foods, rather than their supplements, might be a cost-effective method for long-term use in these patients. In case of finding the beneficial effects of probiotic yogurt consumption in the current clinical trial, its inclusion in the dietary plan of NAFLD patients can be recommended.

*Trial registration* This clinical trial was registered in Iranian Registry of Clinical Trials (www.irct.ir) at 2021-04-19 with code number of IRCT20210201050210N1.

## Background

Non-alcoholic fatty liver disease (NAFLD) is defined as an exacerbation of the triglyceride content in hepatocytes (greater than 5% of liver weight) without excessive alcohol consumption [1]. NAFLD is the most common type of chronic liver disease in the world which might result in simple steatosis, non-alcoholic steatohepatitis (NASH) and fibrosis. These complication can eventually progress to cirrhosis or liver carcinoma [2]. The general prevalence of NAFLD, based on ultrasound screening, is estimated to be 20–30% [3]. In Asia, it has been reported that 15 to 40% of population are affected [4]. According to a meta-analysis, 32% of population in the Middle East and 34% in Iran suffer from this condition [5].

Although weight loss has been the most effective strategy to manage this condition [6–8], dieting for weight loss has had little success in obese people in the long run. Therefore, it is necessary to find complementary therapies to control this condition. The composition of gut microbiota has recently gained great attention in several chronic diseases including fatty liver. Gut microbiota seem to affect this condition through various pathways including increased ethanol production, increased lipopolysaccharide (LPS) release and activating inflammatory cytokines [9, 10]. Therefore, modification of gut microbiota through probiotics might be a new strategy for effective management of NAFLD [11–13]. Earlier studies have shown the efficacy of probiotic supplements in improving levels of liver enzymes [14–17], lipid profiles [14, 18], inflammatory factors [19–21], steatosis [16] and fibrosis [16]. However, due to the high cost of supplements, low access and the possibility of inducing infection and inflammation by their high dosages in long time [14–17], taking probiotics in the context of foods might be a superior choice than supplements. Probiotic foods also contain other nutrients that can be effective in liver health. In addition, findings based on supplements of probiotics may not be generalizable to all patients because of their short-term high dosage use in clinical trials [22–26].

Despite several studies about the effect of probiotic supplements on liver health, limited investigations have assessed the effect of probiotic-enriched foods. In a clinical trial on 102 NAFLD patients, consumption of synbiotic yogurt for 24-week resulted in a significant reduction in liver enzymes and steatosis [27]. Nabavi et al., in a study on 62 patients with NAFLD, administered probiotic yogurt containing Lactobacillus acidophilus and Bifidobacterium for 12 weeks and found a significant reduction in liver fat and enzymes [28, 29]. None of these studies have examined the effect of such interventions on liver fibrosis. In addition, both studies have used ultrasound, rather than fibroscan, to examine liver fat, which might be subject to errors due to subjective decisions. Also, as evidenced in the latest systematic review and meta-analysis, further studies are needed to investigate the effect of probiotics on liver fibrosis, and since studies on probiotic foods are limited. Therefore, the aim of this study was to evaluate the effect of probiotic yogurt consumption on liver enzymes, steatosis and liver fibrosis in patients with NAFLD.

## Patients and methods

### Participants

This study will be a parallel randomized clinical trial (CRT) that will be conducted in Tehran, Iran, in 2021. The sample size was calculated by considering the type 1 error of 5%, the study power of 80% and the hepatic steatosis levels [30] (based on CAP) as a key variable based on data from previous studies. Considering the mean difference in hepatic steatosis levels of 2 dB/mL between the two groups [12], using the suggested formula for parallel clinical trials, we will need 28 patients in each group. However, by taking a possible drop-out of 20% into account, we will recruit 34 patients in each group based on the study inclusion criteria. Outpatients with NAFLD will be recruited from private clinics in Tehran, Iran. The diagnosis of NAFLD will be done by a gastroenterologist based on examination with a fiberoscan. The study is ethically approved by the Bioethics Committee of Tehran University of Medical Sciences, Tehran, Iran, and is registered in the Iranian Registry of Clinical Trials website (http://www.irct.ir).

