### Assessment of hepatic steatosis and fibrosis

Hepatic steatosis and fibrosis among all participants will be examined by transient elastography with fibroscan by the same gastroenterologist at the beginning and end of the study. Patients will be asked to lie down on their back and place the right hand above their head. Then the probe will be placed on the right side of the liver in patients’ intercostal area. The results of liver fibrosis will be expressed as Kilopascal (Kpa). The interpretation of fibrosis assessment results will be based on METAVIR Score [31]. The controlled attenuation parameter (CAP) test will be used to assess steatosis and the results will be reported in dB/m. CAP results will vary between 100 and 400 dB/m.

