### Statistical analysis

In this study, all analyses will be done using SPSS software version 26. Normal distribution of data will be assessed by the application of Kolmogorov–Smirnov test. In case of a non-normal distribution, we will apply logarithmic transformation. Results will be reported as mean ± standard deviations (SD) or medians (interquartile ranges). General characteristics and dietary intake of individuals between the two groups will be compared using independent t-test and chi-square test as needed. Repeated measure analysis of variance (RM-ANOVA) will be used to examine the effects of probiotic yogurt consumption on outcome variables, where we will examine the effects of time, intervention as well as time-group interaction effects. In this analysis, baseline values of outcome variables will be controlled for. We will also perform post hoc tests after ANOVA analysis to examine the variables between study groups. In case of any difference between the two groups in terms of dietary intakes (other than the intervention) and physical activity throughout the study, these differences will be adjusted for in the analysis to reach an independent effect of intervention on study outcomes. Statistical significance will be set to 0.05.

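### The claimed 80% power for a CAP difference of 2 with 28 per group needs an SD of about 2.7 dB/m, which is implausible, and the unit conflicts, so at least one printed input is wrong

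*Protocol article*

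**What the plan says.** The sample-size paragraph (protocol article, Participants) takes hepatic steatosis by CAP "as a key variable based on data from previous studies", with a 5% type 1 error and 80% power. The target effect is given as "Considering the mean difference in hepatic steatosis levels of 2 dB/mL between the two groups". From an unspecified formula for parallel trials it concludes that "we will need 28 patients in each group", raised to 34 for 20% drop-out. No SD and no sidedness are printed. 

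The section on assessment of hepatic steatosis and fibrosis describes the same measure in another unit, "the results will be reported in dB/m", and gives its span: "CAP results will vary between 100 and 400 dB/m". 

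The inclusion criteria require NAFLD confirmed by fibroscan, age 20 to 60 and BMI 25 to 35 kg/m². They state no CAP limits. The Statistical analysis section controls for baseline values of the outcomes and sets the significance level at 0.05.

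**The concern.** Once type 1 error, power, difference and group size are fixed, the two-group formula leaves one unknown, the SD. A missing SD could be put down to condensation in an article. Here, however, the printed figures determine it, and the value they determine does not look like an SD of CAP. This is the only power statement in the article, and it concerns the variable that sizes the trial. If it is wrong, readers are told that the trial has a sensitivity to steatosis changes which the printed inputs do not support.

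**Working it through.** **Inputs from the protocol article.** Type 1 error 0.05, power 0.80, difference 2 and n = 28 per group (Participants); CAP in dB/m from 100 to 400 (Assessment of hepatic steatosis and fibrosis); baseline adjustment (Statistical analysis). Two-sided testing is my assumption, because sidedness is not stated. 

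**Step 1: the plan's own figure.** The 28 cannot be reproduced forwards without an SD, so solve n = 2(z_α + z_β)²SD²/δ² for the SD:

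- Two-sided: SD = 2 × √(28/2) / (1.960 + 0.842) = 7.483 / 2.802 = 2.67.
- Check: 2 × 2.802² × 2.67² / 2² = 27.98, which rounds up to 28.
- Two-sided t test (noncentral t): 28 per group gives 80% power at a standardised difference of 0.7624, so SD = 2 / 0.7624 = 2.62.
- One-sided: 7.483 / (1.645 + 0.842) = 3.01.
- Even a formula that left out the factor 2 for two groups would allow only 2 × √28 / 2.802 = 3.78. 

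**Step 2: against the CAP scale.** With an SD of 2.67, about 95% of patients would lie in a band of 2 × 1.96 × 2.67 = 10.5 dB/m. That is 10.5 / 300 = 3.5% of the range the protocol gives. 

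**Step 3: does baseline adjustment rescue it?** The relevant SD is then the residual one, SD × √(1 − r²), with r the correlation between baseline and week 12. For it to equal 2.67, r = √(1 − (2.67/SD)²):

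| Assumed raw SD (dB/m) | r needed |
|---|---|
| 10 | 0.964 |
| 20 | 0.991 |
| 30 | 0.996 |
| 50 | 0.9986 |

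A change-score reading, with SD × √(2(1 − r)), needs practically the same r: at SD 20, r = 1 − (2.67/20)²/2 = 0.991. 

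**Step 4: power for a true difference of 2 dB/m, 28 per group.** The SDs and correlations are assumptions. Power is two-sided, by noncentral t. The n per group is 2 × 2.802² × SD² / 4, unadjusted.

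| Assumed SD | Power, unadjusted | Power, r = 0.7 | Power, r = 0.9 | n per group for 80% |
|---|---|---|---|---|
| 10 | 11% | 18% | 39% | 393 |
| 20 | 6.6% | 8.1% | 13.5% | 1,570 |
| 30 | 5.7% | 6.4% | 8.7% | 3,532 |
| 50 | 5.3% | 5.5% | 6.3% | 9,812 |

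**Step 5: what 28 completers per group can detect with 80% power.** Unadjusted, 0.7624 × SD: 15 dB/m at SD 20, 23 at SD 30, 38 at SD 50. With adjustment, 0.7624 × SD × √(1 − r²): at r = 0.7, 0.7624 × 20 × 0.714 = 10.9 dB/m for SD 20 and 0.7624 × 50 × 0.714 = 27.2 dB/m for SD 50.

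**The case against.** The strongest reply is that the article gives no CAP SD and points to earlier studies that cannot be seen here, so the documents alone yield no power figure. That stands. A reader might infer that the real power is 5 to 7%. That figure needs an assumed SD of about 18 dB/m or more and an unadjusted comparison, whereas the plan adjusts for baseline. At an SD of 10 the power is 11%, and at an SD of 5 it would be 31%. 

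Second, the printed 2 may itself be a misprint or belong to another scale, and the wrong unit makes this more likely. For illustration only, a difference of 20 dB/m with 28 per group would imply an SD of 20 × √14 / 2.802 = 26.7 dB/m. The documents therefore cannot show whether the trial is underpowered or the sentence is misprinted. This limits the conclusion about the design, but it does not clear the text: the printed power statement is wrong in either case. 

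Third, a reader might say that an SD of 2.7 cannot fit a scale of 100 to 400. That is too strong, because a range of possible results does not fix an SD. The between-patient SD is also not the only relevant one when baseline is controlled for. Implausible is the word the documents support, and Step 3 shows that adjustment does not change it. 

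Finally, nothing in the article says that a null CAP result will be taken to exclude a 2 dB/m effect, so that inference should not be put to the sponsor as fact.

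**Conclusion.** The point holds: the printed inputs agree with one another only at an SD of about 2.7 dB/m (about 3.0 if one-sided). Such an SD is not credible for CAP on the protocol's own scale without stated CAP limits, unless baseline and week-12 values correlate at about 0.99 or more (raw SD 20 or above). Together with the conflict between dB/mL and dB/m, this means that at least one printed input is wrong. The claim of 80% power for a difference of 2 is unsupported and needs correction. 

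Confidence is high for the implied SD and the unit conflict. The size of the power shortfall is conditional. If 2 dB/m is truly intended, power is about 5 to 11% for assumed SDs of 10 to 50 unadjusted, and about 6 to 14% for SDs of 20 to 50 with adjustment at r = 0.9. It does not follow that 34 per group is too few, because the intended difference is not known.

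**What to change.** 1. Check the intended difference against the cited source, and correct its value and its unit (dB/m).
2. State the SD, its source and the sidedness, and recompute the sample size from them.
3. If the difference of 2 dB/m stands, withdraw the claim of 80% power. State instead what 28 completers per group can detect with 80% power: 0.76 SD unadjusted, or 0.76 × SD × √(1 − r²) with baseline adjustment. Put this into dB/m with the sourced SD or with the pooled, blinded baseline SD of the enrolled patients. Enrolment need not change for this.
4. Interpret the CAP result from its confidence interval. 

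The cost is one rewritten paragraph and a check of the source. It can be done although recruitment has started, since the pooled baseline SD needs no unblinding. If 2 dB/m stands, the stated sensitivity will be less favourable than the present text suggests.

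### 34 per group falls slightly short of the plan's own 20% drop-out allowance: keeping 28 on expectation takes 35 per group

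*Protocol article*

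**What the plan says.** The Participants section sets the error rates ("The sample size was calculated by considering the type 1 error of 5%, the study power of 80"%), names CAP-based steatosis as the key variable, and gives the target difference: "Considering the mean difference in hepatic steatosis levels of 2 dB/mL between the two groups". From this it concludes that "we will need 28 patients in each group". It then makes the allowance for losses: "by taking a possible drop-out of 20% into account, we will recruit 34 patients in each group". The Methods paragraph of the abstract gives the matching total: "Sixty-eight patients with NAFLD will be recruited in this study", which is 34 + 34.

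The article prints no formula for the step from 28 to 34. No other section gives a different drop-out rate, evaluable number or recruitment target.

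**The concern.** A drop-out percentage normally describes the share of recruited patients who are lost. To finish with a required number, one therefore divides that number by the share retained. Adding the percentage to the required number gives too few, because 20% of 34 is more than 20% of 28. Here the allowance is meant to secure 28 evaluable patients per group after a 20% loss, and 34 does not do so on expectation.

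What is at stake is whether the sample-size statement is correct on its own figures. A reader would take it that the trial keeps its stated 80% power at its stated loss, and it falls just short of that.

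**Working it through.** **Inputs, all from the Participants section unless noted**
- Evaluable patients needed: 28 per group
- Drop-out: 20%
- Recruited: 34 per group (68 in total, abstract)
- Type 1 error 5%, power 80%. Two-sided testing is an assumption, since sidedness is not stated.
- SD: not stated. The inflation step does not need it.

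**1. Reproducing the plan's figure.**
- Multiplying: n × (1 + d) = 28 × 1.20 = 33.6, rounded up to 34. This matches.
- Dividing: n / (1 − d) = 28 / 0.80 = 35 exactly. This does not match, and no rounding of 35 gives 34.

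**2. What 34 delivers at 20% loss, on expectation.**
- Per group: 34 × 0.80 = 27.2, which is 28 − 27.2 = 0.8 below the need.
- Both groups: 68 × 0.80 = 54.4, against 2 × 28 = 56.
- With 35 per group: 35 × 0.80 = 28.0, and 70 × 0.80 = 56.

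**3. The loss that 34 can absorb.**
- 1 − 28/34 = 6/34 = 17.6%.
- In whole patients within one group, losing 6 of 34 (17.6%) leaves 28, and losing 7 of 34 (20.6%) leaves 27.
- Pooled over both groups, losing 12 of 68 (17.6%) leaves 56, and losing 13 of 68 (19.1%) leaves 55.

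**4. Cost in power.** The plan's claim that 28 per group gives 80% is taken at face value, and power is recomputed at the smaller size. With the noncentral t distribution (two-sided 5%), the standardised difference that gives 80% at 28 per group is 0.762. Holding it fixed:

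| Per group | Power |
|---|---|
| 28 | 80.0% |
| 27.2 | 78.8% |
| 27 | 78.5% |

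The normal approximation agrees. The standardised difference is √(2/28) × (1.960 + 0.842) = 0.749. At 27 per group, 0.749 × √(27/2) − 1.960 = 0.791, and Φ(0.791) = 78.6%.

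**The case against.** Four points on the other side deserve weight.

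- **20% as a ceiling.** The wording "by taking a possible drop-out of 20% into account" can be read as an upper limit. Applied within each group, a ceiling of 20% permits at most 6 losses of 34, because the seventh makes 20.6%, and 28 remain. This stands, and it rules out saying flatly that a 20% loss leaves 27. It does not rescue the figure as an expected rate, where 27.2 is below 28. Nor does it rescue the pooled total, where 19.1% loss already leaves 55 of the 56 needed.
- **The cause is not shown.** No inflation formula is printed, and the unrounded base is not given. If that base lay above 27.0 and not above 27.2 (an assumption), it would be rounded up to 28, and dividing it by 0.80 would give between 33.75 and 34.0, also rounded up to 34. Multiplication is the likelier explanation but is not established. The mismatch between the three printed figures remains either way.
- **The size is small.** A drop-out rate is a rough forecast, and one patient per group would change no conclusion. This stands, and it settles how serious the point is. It does not make the sentence correct.
- **The base is itself unverified.** Without an SD, 28 cannot be checked, so the power figures are conditional on it. This also stands. It is a separate question, and the inflation step is off whatever the SD.

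A reader might go further and infer that the Exclusion criteria section (specific diets, alcohol or tobacco, multivitamin-minerals, medication changes) will take out more patients on top of the 20%, so that power falls well below 79%. The document does not support this. It gives no rate for such exclusions and does not say whether the 20% already covers them.

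**Conclusion.** The point holds as a minor correction. On the plan's own figures, 34 per group does not retain 28 on expectation after 20% loss; 35 would. The shortfall is 0.8 of a patient per group on expectation (54.4 against 56 overall), and power is about 79% (78.5% at 27, 78.8% at 27.2 per group) instead of 80%.

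This rests on reading 20% as the expected share of recruited patients lost, on a two-sided 5% test, and on accepting that 28 per group gives 80%. It should not be read as evidence that the trial is materially underpowered: a loss of 1.2 to 1.5 percentage points does not show that.

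**What to change.** Restate the allowance in the Participants section, for example:

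> Recruiting 34 per group retains 28 with up to 17.6% drop-out (6 of 34); at an expected 20% drop-out about 27 per group remain, with about 79% power at the design effect.

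This costs one sentence and leaves the total of 68 in the abstract as it is. It also remains possible now that recruitment has begun (the Trial status section gives December 2021). If the authors prefer to keep the 20% allowance as an expected rate, the figure consistent with it is 35 per group, 70 in total. That means two more patients and a matching change in the abstract.

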### Inclusion criteria

In this study, we will recruit patients with NAFLD, whom condition was approved by a gastroenterologist using fiberoscan examination. Individuals aged 20–60 years with a body mass index between 25 to 35 kg/m^2^ that have a fixed plan for medication use during the last 3 months will be included in the current study.

### Non-inclusion criteria

We will not include smokers, those with a history of alcohol use, pregnant or lactating women or those planning to get pregnant in the next three months**,** individuals with pathologic conditions affecting the liver, including acute and chronic hepatitis, viral hepatitis, liver transplantation, autonomic hepatitis, hemochromatosis, primary biliary cirrhosis or Wilson's disease, antitrypsin deficiency, thyroid disease and lactose intolerance. In addition, patients who were taking antibiotics and medications affecting serum lipids as well as those taking multivitamin-minerals during the previous month will not be included. Use of any probiotic products during the last two months will be another non-inclusion criteria.

### Exclusion criteria

We will exclude patients who are on a specific diet throughout the study, those who are consuming alcohol and/or tobacco as well as individuals who are taking multivitamin-minerals throughout the study. In addition, any changes in the medications during the study will also be a criterion for exclusion.

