### Study design and intervention

A flowchart of the study design is shown Fig. 1. Flow-diagram of study process is shown in Fig. 2. In the first phase of this study, we will screen 300 patients with NAFLD based on the inclusion criteria mentioned above. Then, those who meet the criteria will be included in the study. All participants will be asked to complete and sign the written informed consent. Before the start of intervention, all study participants will be in a 2-week run-in period, during which four 24-h food recalls (two working days and one non-working day) will be used to collect dietary information. In addition, subjects will be requested to record their physical activity for two days (one working day and one weekend day) during this period. Further information about demographic characteristics, past medical history, medication use as well as socioeconomic status (SES) will be collected in this period through the use of a comprehensive questionnaire in a face-to-face interview. Anthropometric indices, blood pressure, liver enzymes, insulin resistance, hepatic steatosis, liver fibrosis and lipid profile will be evaluated at study baseline. Then study participants will be classified into blocks based on age (20–40/ 40–60 years old), sex (male, female) and BMI (25–30/ 30-35 kg/m^2^). Therefore, the size of each block will be 2 people with the same age, sex and BMI. These participants will then be randomly assigned into intervention and non-intervention groups. Randomization will be done by a third person, who is not aware of the study aims and groups. The first person (say A) in a block will be assigned into the intervention group and the second person (say B) in that block will be assigned into the control group. All participants, study personals and laboratory staffs will be blind to the intervention. Participants in the intervention group will consume 300 g/d of probiotic yogurt containing 10^6^ cfu/g of Lactobacillus acidophilus and Bifidobacterium lactis strains for 12 weeks, while participants in the control group will consume 300 g/d of plain yogurt daily (without any added probiotics) for 12 weeks. Yogurt packages will be distributed to participants every two weeks. The appearance, packaging and taste of yogurts will be the same. Quality control of these yogurts in terms of colony forming units of live bacteria and other nutritional values will be evaluated before the study. In order to comply with the ethical requirements in research, all patients will receive a weight loss diet after ending the study. Participants will be asked not to change their routine lifestyle, dietary habits, and medicines throughout the study. All study outcomes will be examined again at the study end. The study was designed according to the Standard Protocol Items: Recommendations for Interventional Trials (SPIRIT) 2013 shown in Fig. 3.

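### The in-study exclusion criteria, read in the ordinary way, remove randomised patients for events after randomisation, and nothing in the article keeps those patients in follow-up or in the analysis

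*Protocol article*

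**What the plan says.** The article has three eligibility lists. Inclusion criteria cover diagnosis, age, BMI and a stable medication plan over the previous three months. Non-inclusion criteria bar people at entry; that section begins "We will not include smokers, those with a history of alcohol use" and also covers recent multivitamin-mineral use.

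The third list, Exclusion criteria, is worded for the trial period: "We will exclude patients who are on a specific diet throughout the study, those who are consuming alcohol and/or tobacco", then "individuals who are taking multivitamin-minerals throughout the study", and finally "any changes in the medications during the study will also be a criterion for exclusion".

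Under Study design and intervention, "Participants will be asked not to change their routine lifestyle, dietary habits, and medicines throughout the study". The same section says "All study outcomes will be examined again at the study end", without saying whether this covers patients who have met an exclusion criterion.

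Under Statistical analysis, "Repeated measure analysis of variance (RM-ANOVA) will be used to examine the effects of probiotic yogurt consumption on outcome variables". That section also plans to adjust for differences between the groups in diet or physical activity during the study.

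**The concern.** Randomisation makes the arms comparable at allocation. A rule that drops patients for something that happens afterwards compares two selected subsets, and the selection can differ by arm if the event depends on treatment or on the patient's course.

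Medication change is the clearest case. Glucose, insulin, lipids, blood pressure and liver enzymes are all trial outcomes, and worsening in one of them is a plausible reason for a change of medicine. The rule covers any change, with no limit by drug or by reason. The link is weaker for tobacco, alcohol and supplements.

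The trial is small, so a few such removals matter. A week-12 measurement that is not taken cannot be recovered later.

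**Working it through.** **Does the rule reach randomised patients?**

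- Smoking, a history of alcohol use and recent multivitamin-mineral use are already barred at entry. As an entry list, the third list would largely repeat the second.
- A medication change during the study cannot be known at screening, and stability before entry has its own criterion.
- Allocation follows a 2-week run-in and precedes 12 weeks of yogurt. Some exclusions could fall in the run-in, but most of the exposure time comes after randomisation.

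**Does anything keep these patients in?** No section says that excluded patients return for the final assessment or are analysed as allocated. Outcomes are taken at baseline and end only, so a standard repeated-measures ANOVA uses only patients with both values. Diet is handled in two ways: Exclusion criteria removes a patient on a specific diet, while Statistical analysis adjusts for dietary differences.

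**The plan's own figures (Participants section).** 28 evaluable per group, 20% drop-out, 34 recruited per group.

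- 28 × 1.20 = 33.6, rounded up to 34. The stated figure is reproduced. (Dividing, 28 / 0.80 = 35.)
- The 28 cannot be reproduced, because no SD is given for the stated difference of 2.
- The detectable effect therefore has to be back-solved. For a two-sample t-test with 28 per arm, 80% power and a 5% type 1 error (assumed two-sided), noncentral-t power equals 0.80 at d = 0.762 SD. This is the yardstick below.

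**Size of the shift.** The article gives no exclusion rates, so the rates here are assumptions.

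1. *Mild case.* Of 34 in one arm, 5 are removed, and their outcomes average 0.5 SD worse than those retained.
   Shift in that arm's mean = fraction removed × difference = (5/34) × 0.5 = 0.074 SD.
   Relative to the yardstick: 0.074 / 0.762 = 10%.
2. *Worst case at the chosen rates.* Removal picks exactly the worst outcomes, 15% of control and 5% of intervention, with no true effect. Removing the worst fraction p of a standard normal shifts the mean by φ(z)/(1 − p), where z is the (1 − p) quantile.
   p = 0.15: 0.2332 / 0.85 = 0.274 SD.
   p = 0.05: 0.1031 / 0.95 = 0.109 SD.
   Shift in the contrast = 0.274 − 0.109 = 0.166 SD, and 0.166 / 0.762 = 22%.

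**Direction.** In case 2 the control arm is made to look better, which counts against the yogurt. If the intervention arm lost more of its worst patients, the sign would reverse.

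A common removal threshold in both arms does not protect the comparison either. With a true benefit of 0.75 SD and a threshold that removes 5% to 20% of controls, the difference among retained patients falls to between 0.66 and 0.52 SD. This too assumes that removal follows outcome perfectly.

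**The case against.** The strongest reply is that the article says only that patients are excluded. It does not say from what (treatment, follow-up or analysis) and does not mention randomisation. An analysis set or a missing-data rule can properly be left to an analysis plan, so silence on those is not a fault. This is right as far as it goes. The point rests instead on a rule that the article itself fixes. Removal is its ordinary meaning, and no section says otherwise.

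The bias mechanism is also weaker than it first looks. Outcomes are measured only at baseline and end, so no interim trial result prompts a medication change. Entry requires three months of stable medication, and participants and staff are blinded. This stands as a limit on size and likelihood. It does not remove the problem: changes made in outside care remain possible, and blinding does not prevent exclusion that depends on the patient's course.

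Three stronger readings are tempting and not supported:

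- A reader might infer that only compliant completers are analysed. The Adherence section monitors yogurt intake but sets no threshold, and nobody is excluded for not eating the yogurt. The planned dietary adjustment also implies that some patients whose diet departs are meant to stay.
- A reader might infer that the exclusions eat into the sample beyond the drop-out allowance. If they did and left 24 per arm, power at 0.762 SD would fall from 80% to 73%. The Participants section does not say whether exclusions count within the 20%, so this is only a possibility.
- A reader might infer that the patients who worsen are the ones most likely to be removed. The documents make that plausible for medication change and do not show it.

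**Conclusion.** The concern holds in this form: the article sets a rule that, read in the ordinary way, takes randomised patients out for events after randomisation, and it contains nothing that retains them. Following it can bias the comparison in either direction.

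The likely size is modest and uncertain: about 0.07 SD in the mild case and about 0.17 SD in the worst case at the rates chosen, or 10% and 22% of the effect the design can detect. These figures rest on assumed exclusion rates. The upper one also assumes that removal tracks outcome perfectly and runs three times as high in control. The 0.76 SD yardstick is inferred from 28 per arm, because the article gives no SD.

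That the rule removes patients from the analysis as well as from the intervention is the natural reading, not an explicit statement.

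**What to change.** 1. In Exclusion criteria, state that the listed events are recorded by arm as protocol deviations, and that they do not remove a randomised patient from the week-12 assessment or from the primary analysis.
2. In Statistical analysis, state that all randomised patients are analysed in their allocated group, with a suitable method for missing week-12 values. Multiple imputation is one example; other methods would serve.
3. Use the present list only to define a per-protocol sensitivity analysis.
4. Reconcile the specific-diet criterion with the planned adjustment for dietary differences, so that one rule governs a patient whose diet changes.

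The cost is protocol wording, a week-12 visit for patients who deviate, and a short missing-data step. It needs no larger sample. The downside is that patients who deviate may slightly dilute the estimate; the per-protocol analysis would indicate how far results differ without them.
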